## **22 INDEMNITY**

### *Insurance for investigators*

The Principal Investigator will ensure that relevant clinical and laboratory staffs engaged in the study are covered for possible legal actions against the investigators for harm through indemnity insurance schemes, which will be paid for by the project during the study period.

### *Health care Insurance for trial volunteers*

All trial volunteers will be provided with health insurance cover for injury or death related to the trial through insurance schemes.

Vecura Company in Sweden will have an insurance that covers any defect in the production of the DNA vaccine only.

SMI will in the role of sponsor assume the liability for the DNA vaccine and under a separate agreement with the Karolinska Institute its role in the CRADA with Walter Reed Army Institute for the MVA.

## **23 PROTOCOL AMENDMENTS**

The TCC will be responsible for preparing protocol amendments needed by the TaMoVac Steering Committee. Amendments to the protocol will be made only after consultation and

agreement between sponsors and Principal investigators. The only exception is where any of the site PIs considers that a volunteer's safety is compromised without immediate action. All amendments that have an impact on volunteer risk or the study objectives, or require revision of the informed consent document, must receive approval from the relevant ethical committees prior to their implementation.

## **24 PUBLICATION**

It is intended that the results of this study will be published in an appropriate peer-reviewed journal, with the aim of submitting a paper for publication within 6 months of the study's completion.

The TaMoVac Trial Coordinating Committee and Bioject Inc will have 30 days to comment on any manuscript. No other publications, whether in writing or verbally, will be made before the definitive manuscript has been agreed and accepted for publication, without the prior approval of this committee. A final report of the study will be prepared by the Investigators and circulated to the Steering Committee for comments.

The presenting author for the first conference presentation of the main trial results will be one of the Tanzanian principal investigators or their deputy.

Apart from the international publication(s), results from the trial will be presented at various national and international conferences. Regular updates will be provided to the study participants, relevant local authorities as well as local media for wider dissemination.

**Appendix 1: Study Timetable**

| Target day | Week | Visit | Visit purpose                                  | Visit Window                   |
|------------|------|-------|------------------------------------------------|--------------------------------|
|            | -4-8 | V1    | Screening I                                    | 4-8 weeks before V3 enrolment  |
|            | -2-4 | V2    | Screening II + baseline immunogenicity I       | 2-4 weeks before V3 enrolment  |
| 0          | 0    | V3    | Enrolment + DNA I + baseline immunogenicity II | Week 0                         |
| 0          |      | V3A   | 30 min post vaccination                        |                                |
| 0          |      | V3B   | Evening of vaccination day                     |                                |
| 1          |      | V3C   | Day 1 post vaccination                         |                                |
| 2          |      | V3D   | Day 2 post vaccination                         |                                |
| 3          |      | V3E   | Day 3 post vaccination                         |                                |
| 4          |      | V3F   | Day 4 post vaccination                         |                                |
| 5          |      | V3G   | Day 5 post vaccination                         |                                |
| 6          |      | V3H   | Day 6 post vaccination                         |                                |
| 7          |      | V3I   | Day 7 post vaccination                         |                                |
| 14         | 2    | V4    | Follow-up safety (+ immunogenicity)            | 14 days post V3 +/- 3 days     |
| 28         | 4    | V5    | DNA II + Follow-up safety                      | 28 days post V3 +/- 3 days     |
| 28         |      | V5A   | 30 min post vaccination                        |                                |
| 28         |      | V5B   | Evening of vaccination day                     |                                |
| 29         |      | V5C   | Day 1 post vaccination                         |                                |
| 30         |      | V5D   | Day 2 post vaccination                         |                                |
| 31         |      | V5E   | Day 3 post vaccination                         |                                |
| 32         |      | V5F   | Day 4 post vaccination                         |                                |
| 33         |      | V5G   | Day 5 post vaccination                         |                                |
| 34         |      | V5H   | Day 6 post vaccination                         |                                |
| 35         |      | V5I   | Day 7 post vaccination                         |                                |
| 42         | 6    | V6    | Follow-up safety + immunogenicity              | 14 days post V5 +/- 3 days     |
| 56         | 8    | V7    | Follow-up safety                               | 28 days post V5 +/- 5 days     |
| 84         | 12   | V8    | DNA III                                        | 84 days post V3 +/- 7 days     |
| 84         |      | V8A   | 30 min post vaccination                        |                                |
| 84         |      | V8B   | Evening of vaccination day                     |                                |
| 85         |      | V8C   | Day 1 post vaccination                         |                                |
| 86         |      | V8D   | Day 2 post vaccination                         |                                |
| 87         |      | V8E   | Day 3 post vaccination                         |                                |
| 88         |      | V8F   | Day 4 post vaccination                         |                                |
| 89         |      | V8G   | Day 5 post vaccination                         |                                |
| 90         |      | V8H   | Day 6 post vaccination                         |                                |
| 91         |      | V8I   | Day 7 post vaccination                         |                                |
| 98         | 14   | V9    | Follow-up safety + immunogenicity              | 14 days post V8 +/- 3 days     |
| 112        | 16   | V10   | Follow-up safety                               | 28 days post V8 +/- 5 days     |
| 210        | 30   | V11   | MVA I + immunogenicity                         | 126 days post V8 +14 /-28 days |
| 210        |      | V11A  | 30 min post vaccination                        |                                |
| 210        |      | V11B  | Evening of vaccination day                     |                                |
| 211        |      | V11C  | Day 1 post vaccination                         |                                |
| 212        |      | V11D  | Day 2 post vaccination                         |                                |
| 213        |      | V11E  | Day 3 post vaccination                         |                                |
| 214        |      | V11F  | Day 4 post vaccination                         |                                |

|     |    |      |                                   |                                 |
|-----|----|------|-----------------------------------|---------------------------------|
| 215 |    | V11G | Day 5 post vaccination            |                                 |
| 216 |    | V11H | Day 6 post vaccination            |                                 |
| 217 |    | V11I | Day 7 post vaccination            |                                 |
| 224 | 32 | V12  | Follow-up safety + immunogenicity | 14 days post V11 +/- 3 days     |
| 238 | 34 | V13  | Follow-up safety                  | 28 days post V11 +/- 5 days     |
| 322 | 46 | V14  | MVA II + immunogenicity           | 112 days post V11 +14 /-28 days |
| 322 |    | V14A | 30 min post vaccination           |                                 |
| 322 |    | V14B | Evening of vaccination day        |                                 |
| 323 |    | V14C | Day 1 post vaccination            |                                 |
| 324 |    | V14D | Day 2 post vaccination            |                                 |
| 325 |    | V14E | Day 3 post vaccination            |                                 |
| 326 |    | V14F | Day 4 post vaccination            |                                 |
| 327 |    | V14G | Day 5 post vaccination            |                                 |
| 328 |    | V14H | Day 6 post vaccination            |                                 |
| 329 |    | V14I | Day 7 post vaccination            |                                 |
| 336 | 48 | V15  | Follow-up safety + immunogenicity | 14 days post V14 +/- 3 days     |
| 350 | 50 | V16  | Follow-up safety + immunogenicity | 28 days post V14 +/- 5 days     |
| 406 | 58 | V17  | Follow-up immunogenicity          | 84 days post V14 +/- 14 days    |
| 490 | 70 | V18  | Follow-up immunogenicity          | 168 days post V14 +/- 14 days   |

**Appendix 2: TaMoVac I Visit Schedule and CRF Flow Chart**

| Visit Week                            | -4-8        | -2-4        | 0                 | 2         | 4     | 6         | 8         | 12    | 14        | 16        | 30    | 32        | 34        | 46    | 48        | 50        | 58        | 70        |
|---------------------------------------|-------------|-------------|-------------------|-----------|-------|-----------|-----------|-------|-----------|-----------|-------|-----------|-----------|-------|-----------|-----------|-----------|-----------|
| Target day                            |             |             | 0                 | 14        | 28    | 42        | 56        | 84    | 98        | 112       | 210   | 224       | 238       | 322   | 336       | 350       | 406       | 490       |
| Visits                                | V1          | V2          | V3                | V4        | V5    | V6        | V7        | V8    | V9        | V10       | V11   | V12       | V13       | V14   | V15       | V16       | V17       | V18       |
| Visit description                     | Screening 1 | Screening 2 | Enrolment + DNA 1 | Follow-up | DNA 2 | Follow-up | Follow-up | DNA 3 | Follow-up | Follow-up | MVA 1 | Follow-up | Follow-up | MVA 2 | Follow-up | Follow-up | Follow-up | Follow-up |
| Clinical Case Forms                   |             |             |                   |           |       |           |           |       |           |           |       |           |           |       |           |           |           |           |
| CRF Informed Consent Screening        | x           |             |                   |           |       |           |           |       |           |           |       |           |           |       |           |           |           |           |
| CRF 1-I Assessment of Understanding   | x           |             |                   |           |       |           |           |       |           |           |       |           |           |       |           |           |           |           |
| CRF 1-II Risk Assessment              | x           |             |                   |           |       |           |           |       |           |           |       |           |           |       |           |           |           |           |
| CRF 5-III Eligibility Form            |             | (x)         | x                 |           |       |           |           |       |           |           |       |           |           |       |           |           |           |           |
| CRF 5-II Inclusion/Exclusion Form     |             | (x)         | x                 |           |       |           |           |       |           |           |       |           |           |       |           |           |           |           |
| CRF 2-I Visit Contact Form Screening  | x           | x           |                   |           |       |           |           |       |           |           |       |           |           |       |           |           |           |           |
| CRF 3-I Physical Exam Form Screening  | x           |             |                   |           |       |           |           |       |           |           |       |           |           |       |           |           |           |           |
| CRF 5-IV Screening Outcome Form       |             | (x)         | x                 |           |       |           |           |       |           |           |       |           |           |       |           |           |           |           |
| CRF 5-I Basic Demographic Form        | x           |             |                   |           |       |           |           |       |           |           |       |           |           |       |           |           |           |           |
| CRF 2-II Visit Contact Form Enrolment |             |             | x                 |           |       |           |           |       |           |           |       |           |           |       |           |           |           |           |
| CRF 2-III Visit Contact Form          |             |             |                   | x         | x     | x         | x         | x     | x         | x         | x     | x         | x         | x     | x         | x         | x         | x         |
| CRF 3-II Physical Examination Form    |             | x           | x                 | x         | x     | x         | x         | x     | x         | x         | x     | x         | x         | x     | x         | x         | x         | x         |
| CRF 4-II Previous Condition Form      | (x)         | (x)         | x                 |           |       |           |           |       |           |           |       |           |           |       |           |           |           |           |
| CRF 4-I Concomitant Medication Form   | (x)         | (x)         | (x)               | (x)       | (x)   | (x)       | (x)       | (x)   | (x)       | (x)       | (x)   | (x)       | (x)       | (x)   | (x)       | (x)       | (x)       | x         |
| CRF 6-I Adverse Events Form           |             |             |                   | (x)       | (x)   | (x)       | (x)       | (x)   | (x)       | (x)       | (x)   | (x)       | (x)       | (x)   | (x)       | (x)       | (x)       | x         |
| CRF 6-II SAE Reporting Events Form    |             |             |                   | (x)       | (x)   | (x)       | (x)       | (x)   | (x)       | (x)       | (x)   | (x)       | (x)       | (x)   | (x)       | (x)       | (x)       | (x)       |
| Diary Card                            |             |             | x                 |           | x     |           |           | x     |           |           | x     |           |           | x     |           |           |           |           |
| CRF 10-I Vaccine/Reaction Form        |             |             | x                 |           | x     |           |           | x     |           |           | x     |           |           | x     |           |           |           |           |
| CRF 10-II Vaccine Request Form        |             |             | x                 |           | x     |           |           | x     |           |           | x     |           |           | x     |           |           |           |           |
| CRF 8-I Randomization Pharmacy        |             |             | x                 |           |       |           |           |       |           |           |       |           |           |       |           |           |           |           |
| CRF 7-I Subject Status Form           |             |             | x                 | (x)       | (x)   | (x)       | (x)       | (x)   | (x)       | (x)       | (x)   | (x)       | (x)       | (x)   | (x)       | (x)       | (x)       | x         |
| CRF 7-II Protocol Deviation Form      |             |             | (x)               | (x)       | (x)   | (x)       | (x)       | (x)   | (x)       | (x)       | (x)   | (x)       | (x)       | (x)   | (x)       | (x)       | (x)       | x         |
| CRF 11-I Pregnancy Report Form        |             |             | (x)               | (x)       | (x)   | (x)       | (x)       | (x)   | (x)       | (x)       | (x)   | (x)       | (x)       | (x)   | (x)       | (x)       | (x)       | x         |
| CRF 9-IV Hematology Form              | x           |             | x                 | x         | x     | x         | x         | x     | x         | x         | x     | x         | x         | x     | x         | x         | x         | x         |
| CRF 9-V Chemistry Form                | x           |             | x                 | x         | x     | x         | x         | x     | x         | x         | x     | x         | x         | x     | x         | x         | x         | x         |
| CRF 9-VII Urine Analysis Form         | x           |             | x                 |           | x     |           |           | x     |           |           | x     |           |           | x     |           |           | x         | x         |
| CRF 9-VI Serology Form                | x           |             |                   |           |       |           |           |       |           |           |       |           |           |       |           |           |           |           |
| CRF 9-VIII CD4 Count Form             |             |             | x                 |           |       |           |           |       |           |           |       |           |           |       |           |           |           |           |
| CRF 9-I HIV Status Form               | x           |             | x                 |           | x     |           |           | x     |           |           | x     |           |           | x     |           |           | x         | x         |
| CRF 9-III ECG Result Form             |             | x           |                   |           |       |           |           |       |           |           |       | x         |           |       | x         |           |           |           |
| CRF 9-II Pregnancy Result Form        | x           |             | x                 |           | x     |           |           | x     |           |           | x     |           |           | x     |           |           | x         | x         |

## Appendix 3: TaMoVac I Immunization and Lab Flow Chart

|                                                        | Weeks       |                         | -4-8        | -2-4        | 0                 | 2   | 4      | 6   | 8   | 12     | 14  | 16  | 30     | 32      | 34  | 46     | 48      | 50  | 58     | 70     |
|--------------------------------------------------------|-------------|-------------------------|-------------|-------------|-------------------|-----|--------|-----|-----|--------|-----|-----|--------|---------|-----|--------|---------|-----|--------|--------|
|                                                        | Target days |                         |             |             | 0                 | 14  | 18     | 42  | 56  | 84     | 98  | 112 | 210    | 224     | 238 | 322    | 336     | 350 | 406    | 490    |
|                                                        | Visits      |                         | V1          | V2          | V3                | V4  | V5     | V6  | V7  | V8     | V9  | V10 | V11    | V12     | V13 | V14    | V15     | V16 | V17    | V18    |
| Investigations                                         | Amount (ml) | Type and # of tubes     | Screening 1 | Screening 2 | Enrolment + DNA 1 |     | DNA 2  |     |     | DNA 3  |     |     | MVA 1  |         |     | MVA 2  |         |     |        |        |
| Hematology (H)                                  |             |                         |             |             |                   |     |        |     |     |        |     |     |        |         |     |        |         |     |        |        |
| CBC                                                    | 3 ml        | Purple top EDTA         | 3ml         |             | 3ml               | 3ml | 3ml    | 3ml | 3ml | 3ml    | 3ml | 3ml | 3ml    | 3ml     | 3ml | 3ml    | 3ml     | 3ml | 3ml    | 3ml    |
| Biochemistry (BC)                               |             |                         |             |             |                   |     |        |     |     |        |     |     |        |         |     |        |         |     |        |        |
| ALT, bilirubin, Creatinine, glucose                    | 6 ml        | Red top coagulant       | 6ml         |             | 6ml               | 6ml | 6ml    | 6ml | 6ml | 6ml    | 6ml | 6ml | 6ml    | 6ml     | 6ml | 6ml    | 6ml     | 6ml | 6ml    | 6ml    |
| Troponin I                                             | From BC     |                         |             |             |                   |     |        |     |     |        |     |     |        | from BC |     |        | from BC |     |        |        |
| Serology                                        |             |                         |             |             |                   |     |        |     |     |        |     |     |        |         |     |        |         |     |        |        |
| HbsAg, VDRL/TPHA                                       | From BC     | Red top coagulant       | from BC     |             |                   |     |        |     |     |        |     |     |        |         |     |        |         |     |        |        |
| HIV test algorithm                                     |             |                         |             |             |                   |     |        |     |     |        |     |     |        |         |     |        |         |     |        |        |
| HIV ELISA/WB                                           | From BC     | Purple top EDTA         | from H      |             | from H            |     | from H |     |     | from H |     |     | from H |         |     | from H |         |     | from H | from H |
| Immunological tests                             |             |                         |             |             |                   |     |        |     |     |        |     |     |        |         |     |        |         |     |        |        |
| CD4 count                                              | From BC     | Purple top EDTA         |             |             | from H            |     |        |     |     |        |     |     |        |         |     |        |         |     |        |        |
| HLA typing                                             | 8 ml        | Purple top EDTA         |             |             | 8ml               |     |        |     |     |        |     |     |        |         |     |        |         |     |        |        |
| Immunogenicity tests                            |             |                         |             |             |                   |     |        |     |     |        |     |     |        |         |     |        |         |     |        |        |
| Binding and neutralizing Ab. incl. Vaccinia Ab.        | 1x10ml      | Red top coagulant       |             | X           | X                 |     | X      |     |     | X      |     |     |        | X       | X   | X      | X       | X   | X      | X      |
| IFN-gamma ELISPOT, fresh cells                         | 9x10ml      | Green top Na-heparin    |             |             | X                 |     |        |     |     | X      |     |     |        | X       |     | X      | X       |     | X      | X      |
| ICS, fresh cells                                       |             |                         |             |             | X                 |     |        |     |     |        |     |     |        | X       |     |        | X       |     | X      | X      |
| Lymphocyte proliferation assay, fresh cells (optional) |             |                         |             |             | X                 |     |        |     |     | X      |     |     |        | X       |     |        | X       |     | X      | X      |
| ICS multi-colors, cryo-preserved cells                 |             |                         |             |             | X                 |     |        |     |     | X      |     |     |        | X       |     |        | X       |     | X      | X      |
| Optional assays, cryo-preserved cells                  |             |                         |             | X           | X                 |     | X      |     |     | X      |     |     |        | X       | X   | X      | X       | X   | X      | X      |
| Total volume for immunogenicity testing:        |             |                         |             | 100         | 100               |     | 100    |     |     | 100    |     |     |        | 100     | 100 | 100    | 100     | 100 | 100    | 100    |
| Total blood vol.= 1261 ml                       |             |                         | 9           | 100         | 117               | 9   | 9      | 109 | 9   | 9      | 109 | 9   | 9      | 109     | 109 | 109    | 109     | 109 | 109    | 109    |
| Urine                                           |             |                         |             |             |                   |     |        |     |     |        |     |     |        |         |     |        |         |     |        |        |
| Urine for pregnancy test, urine dipstick               | 5 ml        | Sterile urine container | x           |             | x                 |     | x      |     |     | x      |     |     | x      |         |     | x      |         |     | x      | x      |

D= DNA 1, 2, 3, M = MVA 1, 2 each to be given at specified visit; CBC – complete blood count, ICS - intracellular cytokine staining; CTL - cytotoxic lymphocyte assay; Red top=coagulant; Purple top=EDTA; Green top=sodium heparin tubes.

Stored samples will be used for antibody testing. Two weeks after DNA 2 PBMC will be collected for cryo-preservation. Tests using fresh cells will not be performed.

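### Appendix 3 marks the DNA-phase immunogenicity draws on the injection visits V5 and V8, while its own total-blood row and Appendix 1 put them at V6 and V9

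*Protocol*

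**What the plan says.** The flow chart in Appendix 3 has 18 visit columns. V5 is DNA II (week 4), V8 is DNA III (week 12), V6 and V9 follow two weeks after each, V11 is the first MVA (week 30), and V12 is two weeks after that (week 32).

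- The row "Binding and neutralizing Ab. incl. Vaccinia Ab" and the optional cryopreserved-cell row are marked at V2, V3, V5, V8 and V12 to V18.
- The row "IFN-gamma ELISPOT, fresh cells" is marked at V3 (baseline), V8, V12, V14, V15, V17 and V18. The proliferation and multi-colour ICS rows also have their only post-baseline DNA-phase mark at V8.
- The row "Total volume for immunogenicity testing" has 100 ml at V2, V3, V5, V8 and V12 to V18. It therefore agrees with the assay marks.
- The row "Total blood vol.= 1261 ml" is the one that differs. It gives 9 ml at V5 and V8, and 109 ml at V6 and V9.
- The footnote reads "Two weeks after DNA 2 PBMC will be collected for cryo-preservation" and adds that fresh-cell tests will not be done. It does not mention DNA III.

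Appendix 1 describes both V6 and V9 as "Follow-up safety + immunogenicity". It describes V5 as injection plus safety follow-up and V8 as injection only.

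The target-day row of Appendix 3 gives 18 for V5, where Appendices 1 and 2 give 28.

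**The concern.** Two rows of one table, one directly below the other, place the same draws at different visits. The body text does not settle it. Sections 8.6 and 8.9 call V6 and V9 essentially safety visits and refer to the flow chart or visit schedule for the blood to be drawn. Sections 8 and 8.1.5 name Appendix 3 as the laboratory schedule and the source for blood volumes. A site working from the marks would draw on the injection day.

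A sample taken on the day of DNA III cannot show the response to that dose. Under the marks the next sample of any kind is V12, after the first MVA. The response to the complete DNA prime, before boosting, would then go unmeasured in all 120 volunteers and could not be recovered later. The protocol reports this quantity from earlier trials. Section 4.8 says two DNA regimens differed after priming but could not be told apart after one MVA. Section 4.6.1 gives the ELISPOT response after three DNA/placebo injections in the preceding Tanzanian trial as 23 of 59 (39%).

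**Working it through.** **Inputs, all from Appendix 3.** Blood count 3 ml and biochemistry ("ALT, bilirubin, Creatinine, glucose") 6 ml at V1 and at V3 to V18; HLA typing 8 ml at V3; immunogenicity 100 ml where the 100 ml row has an entry.

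**Step 1: reproduce the stated total.** Summing the total-blood row: V1 9 + V2 100 + V3 117 + V4 9 + V5 9 + V6 109 + V7 9 + V8 9 + V9 109 + V10 9 + V11 9 + seven visits (V12 to V18) × 109 = 498 + 763 = 1261 ml. The figure reproduces.

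**Step 2: rebuild each visit from its components.** Visit volume = blood count + biochemistry + HLA + immunogenicity entry. Fourteen of 18 visits agree with the total-blood row. The other four are:

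| Visit | Week | Rebuilt from the marks | Total-blood row |
|---|---|---|---|
| V5 (DNA II) | 4 | 3 + 6 + 100 = 109 | 9 |
| V6 | 6 | 3 + 6 + 0 = 9 | 109 |
| V8 (DNA III) | 12 | 3 + 6 + 100 = 109 | 9 |
| V9 | 14 | 3 + 6 + 0 = 9 | 109 |

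The rebuilt volumes also sum to 1261 ml, so checking the grand total cannot reveal the conflict.

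**Step 3: move the two draws.** With the 100 ml entries moved from V5 to V6 and from V8 to V9, all 18 visits match the total-blood row and the sum stays at 1261 ml.

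**Step 4: compare with the other sources.** Appendix 1 supports V6 and V9. The footnote supports V6 only. The V5 marks (antibody and cryopreserved cells, no fresh-cell assay) are what the footnote describes for two weeks after DNA II. The case for V9 rests on the total-blood row and Appendix 1.

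**Step 5: what the marks would cost.** Following the marks, ELISPOT is taken at V8 (week 12) and next at V12 (week 32), a gap of 32 − 12 = 20 weeks. With the draw at V9 (week 14) the gap is 32 − 14 = 18 weeks. The misplacement itself is therefore two weeks, but those two weeks decide whether the sample comes before or after a response to DNA III can appear. It affects 1 of 7 ELISPOT time points and 2 of 11 antibody and optional-PBMC time points.

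**Step 6: the target day.** Week 4 × 7 = 28 days, as in Appendices 1 and 2. The entry of 18 does not fit its own week header.

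**The case against.** The strongest objection is that this may be a table-reading artefact and not an error in the plan. The fully populated total-blood row is coherent, and the sparse rows are displaced by one column at exactly two places. An author with 100 ml at V5 and V8 would be unlikely to write totals that are right only for V6 and V9. That the HIV and urine rows sit on V5 and V8 proves little, because they belong there.

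This stands in part: a column shift cannot be excluded without the original page. Against it, other sparse rows of the same table land on the right non-injection visits. Troponin is at V12 and V15, and fresh-cell ICS includes V12 and V15. The assay marks from V12 onward also agree with the total-blood row. The conflict holds on the text as given, and looking at the page would settle it.

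A second objection is that response to the prime alone is of limited interest. Section 4.8 also says it did not predict the response after boosting, and it frames the question as the net effect after two MVA boosts. The 39% in section 4.6.1 is a preliminary, still-blinded figure from another trial and is not set as a benchmark here. Both points are fair. They limit the importance of the lost sample but do not remove the contradiction.

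A reader might infer that nothing would be measured after three DNA doses. The documents do not support that: ELISPOT is still marked at V12, V14, V15, V17 and V18, all after MVA. Nor should the 20-week gap be blamed on the misplacement, since 18 of those weeks remain once it is corrected.

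**Conclusion.** The point holds as an internal contradiction in an operational sampling chart. The assay marks and the 100 ml row put two draws at V5 and V8; the total-blood row and Appendix 1 put them at V6 and V9. The second reading makes all 18 visit volumes agree, where the first leaves four wrong.

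If the marks were followed, the response to the three-dose prime before the boost would be lost. It might be inferred that the main analysis is at risk. It is not: section 20 sets the primary endpoint two weeks after the second MVA (V15), and section 20.5 makes its formal comparisons at baseline and two weeks after the last immunization. The correction is worth making before sites use the chart, but it does not bear on the trial's primary conclusion.

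This rests on two assumptions: that the printed page shows the same columns as the extracted text, and that sites follow Appendix 3 at V11. Appendix 1 lists immunogenicity at V11, which would give a sample on the day of the first MVA, but Appendix 3 has no mark there and only 9 ml in its total-blood row. The two appendices also differ at V4 (bracketed in Appendix 1) and V13 (Appendix 3 only). Those are separate mismatches, where the Appendix 3 rows agree with one another.

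**What to change.** Check the original page of Appendix 3 for a column shift. If the printed table shows the same placement, move the DNA-phase assay marks and the 100 ml entries from V5 to V6 and from V8 to V9, so that they agree with the total-blood row and Appendix 1. If the printed table already has them at V6 and V9, these marks need no change.

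Reconcile the V5 target day (18 in Appendix 3, 28 in Appendices 1 and 2).

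The cost is a corrected flow chart. Total blood stays at 1261 ml, and no visit or assay is added.
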